## Abstract

**Introduction:**

Fatigue is one of the most common and disabling symptoms in end-stage kidney disease, particularly among in-centre haemodialysis patients. This two-arm parallel group feasibility randomised controlled trial will determine whether a fully powered efficacy trial is achievable by examining the feasibility of recruitment, acceptability and potential benefits of a cognitive-behavioural therapy (CBT)-based intervention for fatigue among in-centre haemodialysis patients.

**Methods:**

We aim to recruit 40 adult patients undergoing in-centre haemodialysis at secondary care outpatient dialysis units, who meet clinical levels of fatigue. Patients will be randomised individually (using a 1:1 ratio) to either a 4–6 weeks’ CBT-based intervention (intervention arm) or to a waiting-list control (control arm). The primary feasibility outcomes include descriptive data on numbers within each recruiting centre meeting eligibility criteria, rates of recruitment, numbers retained postrandomisation and treatment adherence. To assess the potential benefits of the cognitive-behavioural therapy for renal fatigue intervention, secondary self-report outcomes include measures of fatigue severity (Chalder Fatigue Questionnaire), fatigue-related functional impairment (Work and Social Adjustment Scale), sleep quality (Pittsburgh Sleep Quality Index), depression (Patient Health Questionnaire-9) and anxiety (Generalised Anxiety Disorder-7). Changes in fatigue perceptions (Brief Illness Perception Questionnaire), cognitive and behavioural responses to fatigue (Cognitive and Behavioural Responses to Symptoms Questionnaire), sleep hygiene behaviours (Sleep Hygiene Index) and physical activity (International Physical Activity Questionnaire–short form) will also be explored. These self-report measures will be collected at baseline and 3 months postrandomisation. Nested qualitative interviews will be conducted postintervention to explore the acceptability of the intervention and identify any areas in need of improvement. The statistician and assessor will be blinded to treatment allocation.

**Ethics and dissemination:**

A National Health Service (NHS) Research Ethics Committee approved the study. Any amendments to the protocol will be submitted to the NHS Committee and study sponsor.

**Trial registration number:**

ISRCTN91238019;Pre-results.

Strengths and limitations of this studyThis is the first feasibility trial assessing the feasibility, acceptability and potential benefits of a psychological intervention for the management of fatigue among in-centre haemodialysis patients.The mixed-methods approach will help to evaluate comprehensively and in-depth the feasibility and acceptability of the cognitive-behavioural therapy for renal fatigue (BReF) intervention; the qualitative data will complement the quantitative findings and help to identify areas in need of improvement.The BReF intervention was developed systematically, using theory and evidence, with substantial input from patient and public representatives.As this is a feasibility trial, it is not powered to detect efficacy.

## Introduction

End-stage kidney disease (ESKD) is a chronic disease of the kidneys, characterised by inadequate renal functioning, where renal replacement therapy (RRT) is necessary to sustain life.^1^ Haemodialysis (HD) is the most common RRT modality, filtering toxins out of the blood via an artificial extracorporeal blood circuit. A typical HD patient will be required to attend dialysis sessions three times a week for 3–4 hours each time.^2^ On average, patients with renal disorder experience 14 symptoms, with fatigue emerging as one of the most persistent and debilitating symptoms.^3 4^ Fatigue is a complex and subjective symptom characterised by extreme and persistent tiredness resistant to rest and recuperation.^5–7^ Forty-nine to 92% of dialysis patients suffer from fatigue.^3^ Fatigue is a substantial contributor to impaired functioning and quality of life, and recent evidence suggests that it has also implications for clinical outcomes^8–14^; yet, it is often under-recognised and undertreated by healthcare professionals, perceived as a normal consequence of the illness and treatment burden.^15 16^

Current management in the form of pharmacological treatments or exercise is ineffective^17 18^ and no theory-driven and evidence-based psychological interventions aimed at fatigue for this group currently exist, although there is some promising evidence for some improvements in fatigue following psychological interventions not aimed at fatigue specifically.^19^ As the aetiology of fatigue in patients with renal disorder is still largely unknown, no consistent treatment model exists.^8 20^

There is increasing recognition regarding the importance of psychological factors in the perpetuation and maintenance of fatigue in other long-term physical conditions.^21–26^ For example, in multiple sclerosis (MS), negative fatigue beliefs, such as catastrophising about the consequences of fatigue, embarrassment about fatigue and belief that fatigue is a sign of physical damage; and unhelpful behaviours in response to fatigue, like excessive resting or overdoing things followed by long resting periods to recover; were found to be strongly associated with fatigue, above and beyond the role of demographic and clinical factors, such as neurological impairment and remission status.^22^ On the other hand, social support may act as a buffer to fatigue perpetuation.^27^ An understanding of the contribution of these factors to fatigue has translated into successful psychological interventions, leading to clinically significant improvements in fatigue severity and fatigue-related functional impairment.^28 29^ There is, in fact, extensive evidence in support of cognitive-behavioural therapy (CBT) for adjustment and the management of symptoms, like fatigue, in the context of long-term physical conditions, such as cancer and MS,^30 31^ despite being originally developed for the treatment of mood disorders.^32 33^ CBT is a structured, tailored and time-limited talking therapy that focuses on changing negative beliefs and unhelpful behaviours, as well as relaxation techniques, stress management and mindfulness to foster resilience.^33 34^

We conducted preliminary work, consisting of prospective and qualitative studies, which revealed the importance of cognitive and behavioural factors in the experience of fatigue in ESKD, in line with the findings from other long-term physical conditions. To date, the effectiveness of CBT specifically for fatigue has not been examined in this population, yet, a similar approach may also be useful here. Based on the findings from these precursor studies and patient and public involvement (PPI) input, we adapted an existing CBT approach initially developed by one of the authors ([name]) for fatigue in MS. According to this renal fatigue treatment formulation, which integrates biological and psychosocial factors; there are a number of factors that may act as triggers of fatigue in this patient population, such as anaemia and HD. While these factors trigger initial symptoms of fatigue, one’s thoughts, emotions and behaviours in response to fatigue may maintain and perpetuate fatigue, potentially leading to a vicious cycle of negative illness and fatigue beliefs, increased distress and maladaptive behaviours, as displayed in figure 1. The factors maintaining and perpetuating fatigue are targeted in CBT.

**Figure 1. F1:**
[figure not shown]
Cognitive-behavioural therapy model of renal fatigue. This diagram illustrates the different clinical, social situational and psychological factors that contribute to fatigue in this setting.

### Objectives

A feasibility design was deemed necessary to determine whether a full-scale randomised controlled trial (RCT) is feasible, by considering numbers meeting eligibility criteria, rates of recruitment and retention postrandomisation, floor/ceiling effects that might affect sensitivity to change; as well as by identifying any intervention-specific issues, particularly occurrence of adverse events and timing burden. The following aims will be addressed in this feasibility RCT:Objective 1: to estimate rates of recruitment and retention.Objective 2: to estimate willingness to be randomised.Objective 3: to explore the level of adherence to the intervention (intervention arm only).Objective 4: to estimate the standard deviation (SD) of fatigue in this patient population in order to compute a more robust estimate of the sample size required for an efficacy trial.Objective 5: to preliminary assess the psychometric properties of the self-report instruments used.Objective 6: to explore the potential benefits of the intervention at reducing fatigue severity and fatigue-related functional impairment as compared with the waiting-list control.Objective 7: to explore the potential benefits of the intervention at reducing depression and anxiety and improving sleep quality as compared with the waiting-list control.Objective 8: to examine change in fatigue-related cognitions and behaviours, and whether their effect differs between the intervention and control arm.Objective 9: to qualitatively explore patient perceptions of the acceptability and usefulness of the intervention and identify areas of improvement for a future full-scale trial.Objective 10: to explore any intervention-specific issues, particularly setting, mode of delivery of the intervention and acceptable number of sessions/chapters.

## Methods

### Design

A two-arm parallel group feasibility RCT. There will be one follow-up assessment at 3-month postrandomisation. A nested-qualitative study will evaluate patients’ experiences with the intervention.

### Setting and participants

Outpatient HD patients will be recruited from two National Health Service (NHS) sites in England.

### Inclusion and exclusion criteria

Participants are eligible for the study if they:are >18 years of agehave a confirmed ESKD diagnosisare experiencing clinical levels of fatigue defined as scoring >18 on the Chalder Fatigue Questionnaire (CFQ), when using the continuous scoring^35 36^have full verbal and written proficiency in Englishare receiving in-centre HDlength of time on dialysis >90 daysare willing and able to take part in the study and intervention.

Patients will be excluded if they:do not provide informed consent or refuse to be randomisedhave any known cognitive impairmentshave a severe mental health disorder, for example, psychosis and bipolar disorderdo not have full verbal and written proficiency in Englishare currently receiving psychotherapyare currently participating in any other intervention trialare failing on dialysis and approaching end of life (supportive care/palliative care pathway)have a fatigue (CFQ) score below the cut-off at the prerandomisation assessment (spontaneous improvement after screening).

Patients will not be screened for anaemia. Levels of haemoglobin and haematocrit are generally maintained within recommended ranges.^17^ Additionally, there is evidence for a ceiling effect of anaemia management on fatigue^37^ and improvements in fatigue are often below a clinically meaningful threshold, particularly in patients on dialysis.^38^ Nonetheless, the role of anaemia-related factors will be examined in the exploratory analysis and may lead to changes to the inclusion/exclusion criteria for a future efficacy trial.

### Flow of recruitment and participant timeline

Recruitment will take place from October 2017 to July 2018. Patients interested in participating will be given a participant information sheet, screening questionnaire, consisting of sociodemographic and illness-related questions and the CFQ; an informed consent form and a freepost envelope. Potential participants will be given a minimum of 24 hours to establish if they would like to take part. Following consent, eligible participants will receive the baseline questionnaire, and will be randomised after the completion of the baseline questionnaire. Participants who score below the fatigue cut-off at the prerandomisation assessment will be excluded.

Participants will be informed of the outcome of the randomisation process over the phone and will receive confirmation of their treatment allocation and materials via post. We anticipate the participant’s journey through the study will last approximately 4–5 months, as summarised in figure 2, with approximately 1 month dedicated to screening and randomisation. The intervention will last between 4 and 6 weeks, depending on each participant’s needs. Participants are expected to complete one session per week. Follow-up data will be collected at 3 months postrandomisation (T1). On completion of the postintervention questionnaire, a subsample of participants will be invited to take part in the qualitative interview. After completion of follow-up assessments at T1, participants in the control condition will receive the intervention manual and tasks workbook via post.

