**Figure 2 F2:**
[figure not shown]
Anticipated flow of participants through the study. Number of patients approached for screen, those who consented, and those who were assessed for eligibility will be recorded. Eligible patients will be invited to complete a baseline questionnaire (T0). After completion of the baseline questionnaire, participants will be randomised. Participants in the intervention arm will receive the intervention over 4–6 weeks. All participants will complete a follow-up questionnaire at 3 months postrandomisation (T1). Participants in the intervention arm will be invited to take part in a qualitative evaluation interview at the end of their involvement in the study. After completion of the follow-up questionnaire, participants in the control arm will receive the intervention materials.

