### Qualitative interviews

To complement the quantitative process evaluation and further explore the acceptability of the intervention, in line with current MRC process evaluation guidelines,^80^ qualitative interviews will be conducted with a subgroup of participants from the intervention group at 3 months postrandomisation (T1). The interviews will be semistructured and will be conducted over the phone or face-to-face, in a private environment. The interviews will be conducted by an independent researcher, who has not been involved in the intervention delivery. The main aim of the interviews will be to gather participants’ experiences of the intervention, to identify areas of improvement. Purposive maximum variation sampling will be employed to ensure variability of the sample across a range of sociodemographic and clinical characteristics,^81^ in particular: age, gender, ethnicity, dialysis vintage, degree of adherence to the intervention, degree of improvements in outcomes following the intervention. A minimum of 10 interviews will be conducted, until data saturation is reached, meaning the point where no new data is obtained with every new interview.^82^

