### Sample size

The renal service of King’s College Hospital has approximately 550 patients on HD and Lister Hospital has approximately 510 patients on HD, in which we expect to be able to approach 636 (60%) during the recruitment period. Past psychological research in patients on dialysis, conducted by the team, suggest consent rates between 50% and 70%, assuming a more conservative uptake of 40%, 254 patients are expected to be screened, with approximately 30% (n=76) expected to meet the inclusion criteria, including around half reporting clinical levels of fatigue.^59^ Assuming 50% of those eligible will consent to be randomised (n=38), a sample size of 40 participants would allow us to estimate the true population consent rate with a 11% margin of error (95% binomial exact confidence level) for those meeting eligibility criteria. In line with recommended sample sizes of pilot feasibility trials,^83–85^ 40 patients is deemed sufficient to explore feasibility, acceptability and potentially efficacy of the intervention, assuming retention rates of 80%, the true population consent rate will be with a margin of error of 13% (95% binomial exact CI), an acceptable level of error, based on the time, budget and workforce constraints, as FP will act as both the trial coordinator and therapist.

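### As worded, the interview plan gives no route to intervention participants who do not return the 3-month questionnaire, so their views on acceptability may be missed

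*Protocol article*

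**What the plan says.** The protocol article describes the interview invitation in three places.

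- Flow of recruitment and participant timeline: "On completion of the postintervention questionnaire, a subsample of participants will be invited to take part in the qualitative interview".
- Figure 2 caption: "Participants in the intervention arm will be invited to take part in a qualitative evaluation interview at the end of their involvement in the study".
- Qualitative interviews: interviews are held "with a subgroup of participants from the intervention group at 3 months postrandomisation (T1"). Sampling is purposive, for maximum variation. Besides four demographic and clinical characteristics it names "degree of adherence to the intervention, degree of improvements in outcomes following the intervention". Whether a participant was retained to T1 is not on the list. On numbers: "A minimum of 10 interviews will be conducted, until data saturation is reached".

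The interviews serve objective 9, which is "to qualitatively explore patient perceptions of the acceptability and usefulness of the intervention and identify areas of improvement for a future full-scale trial", and under the Analysis plan they also feed objective 10.

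Three other provisions bear on the point. The randomisation and blinding section has missing questionnaires chased by email or telephone and by an assisted visit at the dialysis unit. The Analysis plan has reasons for drop-out logged and reported at each stage. Adherence is described session by session.

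**The concern.** The timeline section makes the invitation follow a completed T1 questionnaire, and one sampling criterion cannot be scored without T1 data. Neither that section nor the Qualitative interviews section gives a route to interview for someone who leaves the study or never sends T1 back. A researcher following the timeline section would not invite such a person; one following the Figure 2 caption could.

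In a feasibility trial this touches a main output. The interviews are the method for objective 9, and intervention-specific issues help to decide whether an efficacy trial goes ahead and in what form. People who found the programme too burdensome could plausibly be among those lost by T1. A frame limited to T1 returners narrows the variation that the chosen sampling method is meant to capture.

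**Working it through.** **Inputs.** Planned total 40 (Abstract; Sample size). Allocation 1:1 (Randomisation, allocation concealment and blinding). Retention 80% (Sample size). At least 10 interviews (Qualitative interviews). I assume that the overall 80% applies equally to both arms and that retention means returning T1.

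**Step 1: the plan's own figure.** The Sample size section attaches a 13% margin of error (95% exact binomial) to 80% retention. With 0.80 × 40 = 32 retained, the exact interval for 32/40 is 64.4% to 90.9%. Half-width = (90.9 − 64.4)/2 ≈ 13.3%, so the figure reproduces. The section words it as a margin on the consent rate, although the number fits the retention proportion; that is a separate matter.

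**Step 2: how many fall outside the frame.** Intervention arm = 40/2 = 20. Non-returners = 20 × (1 − retention).

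| Retention | Non-returners | Returners |
|---|---|---|
| 90% | 2 | 18 |
| 80% (plan) | 4 | 16 |
| 70% | 6 | 14 |

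In every row the returners exceed the minimum of 10 interviews. The target can therefore be met without any non-returner, and the shortfall would not show itself.

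**Step 3: what the condition does.** If only T1 returners are invited, the chance that the interviews include none of the 4 non-returners is 100%. If all 20 could be invited and 10 were drawn at random, it would be C(16,10)/C(20,10) = 8,008/184,756 = 4.3%. The real sampling is purposive and invitees may decline, so this shows only that the invitation rule, and not the small number of interviews, shuts non-returners out.

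**Step 4: the three descriptions applied to each kind of participant.**

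| Intervention participant | Timeline section | Qualitative interviews section | Figure 2 caption |
|---|---|---|---|
| Attends sessions, returns T1 | Invited | In the frame | Invited |
| Stops sessions, returns T1 | Invited | In the frame, sought through the adherence criterion | Invited |
| Attends sessions, T1 not returned | Not invited | No stated bar, but improvement cannot be scored | Can be read as invited |
| Leaves the study before T1 | Not invited | Interview set at T1; improvement cannot be scored | Can be read as invited |

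The descriptions agree on the first two rows and part on the last two.

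**Step 5: direction.** If acceptability were summarised as a proportion, the returner-only value would differ from the whole-arm value by (1 − retention) × (rate in returners − rate in non-returners). At 80% retention the first factor is 0.20. The documents give neither rate. The difference is zero if the rates are equal, and its sign follows the reason for loss. The planned analysis is thematic and yields no such proportion, so I put no percentage on the bias.

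**The case against.** The best defence is that the timeline section describes a sequence. It does not say that only T1 returners may be invited, and nowhere are non-returners called ineligible. The section that defines the interviews sets no completion condition, and a missing value on one of six sampling characteristics excludes nobody. The Figure 2 caption mentions the interview after the T1 questionnaire, so all three places may intend the same thing. Missing questionnaires are actively pursued, in patients who attend the unit regularly. Poor tolerance would also appear in the attendance, task-completion and retention data, which the interviews complement. Finally, an article may leave recruitment detail to the full protocol.

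Much of this stands, and it limits the point. It does not remove it: the article does state when the invitation is issued, that wording reaches returners only, and the plan still allows for 20% loss after its reminders.

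A reader might infer three stronger things, none of which the documents support.

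- That everyone who drops out goes unheard. People who stop therapy but return T1 are eligible, and the adherence criterion seeks them out.
- That the reasons for attrition are hidden. The Analysis plan has them recorded and reported, although a logged reason is not a semistructured interview.
- That acceptability will look better than it is, by a stated number of points. Loss in this population may have nothing to do with the intervention, and no acceptability percentage will be produced.

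**Conclusion.** The point holds in a narrow form. Followed literally, the timeline section leaves about 4 of 20 intervention participants without an interview route at the assumed 80% retention (2 at 90%, 6 at 70%), while the Figure 2 caption can be read as including them. The count is all-cause loss and rests on equal retention in the two arms; the documents do not attribute any of it to the intervention being unacceptable. What would be missed is non-returners' in-depth account of the programme. That may tilt the objective 9 themes towards those who tolerated it, by an unknown amount that could be nil. No sample size or quantitative analysis is affected. This is a cheap improvement to the plan and not a flaw that undermines the trial.

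**What to change.** Reconcile the timeline section, the Figure 2 caption and the Qualitative interviews section as follows.

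1. State that any intervention participant may be invited to interview at the end of their involvement, including one who stops early or does not return T1, unless consent to contact has been withdrawn.
2. Add retention status (T1 returned or not) to the purposive sampling characteristics. Set no fixed quota: with about 4 such people, some of them possibly fully withdrawn, a quota may be unattainable and has no basis in the document.
3. Use degree of improvement as a sampling characteristic only where T1 data exist.
4. Report how many non-returners were invited and how many were interviewed, so that readers can judge how far the themes cover them.

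The cost is wording plus a few extra invitations. The independent interviewer is already in place and telephone interviews are already allowed. The downside is that some of those invited will decline, so the gap may be narrowed without being closed.
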